## Methods/design

This protocol is reported following the Standard Protocol Items: Recommendations for Interventional Trials (SPIRIT) criteria [38]. For the completed SPIRIT Checklist see Additional file 1.

### Study setting

The study has 30 clusters in two operational districts (ODs) (one OD includes the jurisdiction of 10 health centers (HC) or roughly 100,000–200,000 individuals) within Kampong Cham province. Each cluster has on average 200 HHs or 1000 individuals. The rainy season runs from April to November, and the peak dengue season is from May to July. Kampong Cham was selected as it has one of the highest dengue incidence rates of 1.6 cases per 1000 people in Cambodia and the environmental characteristics are similar to most dengue-endemic areas of Cambodia (personal communication, [name], 2016). The clusters (containing one or more villages) were selected based on availability of entomological surveillance data from previous surveys. To avoid spillover effects, clusters had to be at least 200 m from the nearest HH outside the cluster since *Ae. aegypti* in this region have an average flight range of 50–100 m [39] (see Fig. 1).

**Fig. 1 Fig1:**
[figure not shown]
Example of a 200-m boundary around selected clusters

#### Eligibility criteria

Every house within the cluster boundaries will be invited to participate in the trial.

#### Interventions

Selected villages will be randomized into one of three study arms (see Table 1). Study arm 1 receives all three interventions, while study arm 2 receives only guppies and COMBI activities, and arm 3 will receive only the standard vector-control activities from the Ministry of Health. The total trial period for the interventions will be 11 months (see Figs. 2 and 3).

**Table 1 Tab1:** Interventions randomized to each study arm

Intervention	Arm 1	Arm 2	Arm 3
Guppy fish in key containers (>50 L)	X	X	
Communication for Behavior Impact (COMBI) activities	X	X	
Direct pyriproxyfen (PPF) application (Sumilarv® 2MR) in smaller containers (10–50 L)	X

**Fig. 2 Fig2:**
[figure not shown]
Flow chart of cluster selection. Selection of clusters in Kampong Cham, Cambodia

**Fig. 3 Fig3:**
[figure not shown]
Standard Protocol Items: Recommendations for Interventional Trials (SPIRIT) with schedule of enrollment, interventions, and assessments

Study arm 1 was chosen to evaluate the effectiveness of all three interventions in combination. Application of any insecticide can be expensive when taking into account procurement and operational costs. Arm 2 was selected to evaluate the effectiveness of less expensive interventions (guppies and COMBI), although all strategies are expected to be less expensive than current strategies. As COMBI-related activities have been shown to have a significant impact on the coverage of interventions in Cambodia and elsewhere [21, 22, 34] a guppy-only arm was not included. Therefore, the trial will not give separate estimates of the effects of guppies and COMBI. Larvicide-only arms were not included because larvivorous fish are more sustainable and cost-effective than larviciding [16, 17, 21, 22, 40, 41], and if larviciding was found to be equally effective, guppies would be recommended in terms of cost and acceptability.

### Guppies

In rural Cambodia, more than 80% of *Aedes* mosquito breeding is detected in key containers, such as large water jars, cement tanks and other large containers, used for the storage and collection of water for human and animal consumption and washing [20]. To target these containers, two guppy fish (*Poecilia reticulata*) will be placed into each water container with a volume greater than 50 L in intervention villages (arms 1 and 2). This is based on larval consumption of guppies determined by Seng et al. [21] and past experiences using guppies in vector control in Cambodia [22]. The guppy fish will be distributed after the baseline activities through a local community network managed by provincial government authorities. Guppy banks will be set up at the corresponding health centers and consist of twenty 500-L jars. Guppy banks will be colonized and can provide fish at any time to CHWs in implementation villages. One CHW will be assigned to monitor 30 HHs each month. They will each have two 500-L jars which they can colonize with guppies to provide for their assigned HHs. When CHWs need more guppies they can return to the guppy bank for them. Each month CHWs will conduct visual checks and ensure that all their assigned HHs have guppies in all large containers, and replace them if necessary. Adult guppies are on average 1.5–3.5 cm long (males) or 3–6 cm long (females) [42].

### Pyriproxyfen matrix release (Sumilarv® 2MR)

Each device or disk (See Fig. 4) is designed to provide coverage for 40 L of water. It is also possible to cut disks into smaller sizes for smaller-sized containers (see Table 2).

**Table 2 Tab2:** Dosage application rate of Sumilarv® 2MR disks (target dosage is one disk per 40 L)

Container capacity, L	Number of 2MR disks	Target ppb
10	1/5	27
20	½	27
30	2/3	27
40	1	27
50	1	27

*ppb* parts per billion

**Fig. 4 Fig4:**
[figure not shown]
Sumilarv® 2MR disk (5-cm radius)

PPF devices will be distributed after the baseline survey in the same manner as described above, and replaced after 6 months. Additional devices will be left at the health center for CHWs to distribute during their monthly monitoring visit if some have been lost or need to be replaced.

Although there have not been any studies evaluating the safety of PPF in humans, toxicity to fish is induced at 450 ppb, which is approximately 45 times greater than the target ppb (10) of Sumilarv® 2MR [43]. The LD50 in rats is 5,000,000 ppb, or 500,000 times the target concentration [44]. These data suggest a very favorable mammalian toxicity profile, and extremely low risk for humans using this product.

### Communication for behavioral impact activities

An initial rapid assessment consisting of FGDs and In-depth Interviews (IDIs) regarding knowledge, attitudes, and behaviors of community members was completed. The results were used in a message and material development workshop held with key community and district stakeholders. During this meeting the community helped to develop behavior change communication materials and come up with key messages. The results were used to understand the common social gathering locations for health education sessions, culturally appropriate channels of communication, and to create communication materials: flip charts to guide CHW education sessions, posters and banners for display in the villages, songs, and CHW materials such as hats, t-shirts, bags, and rain coats.

A 2-day training will be given to CHWs on communication and facilitation skills, following which they will take the lead role in conducting health education sessions in their community. A monthly meeting will also be conducted with CHWs to assess progress, address issues and challenges, and provide them with continuous training to develop their confidence and skills. The health education sessions will occur twice per month and will be participatory, as Khun and Manderson [28] found that health education sessions, where participants actively identify breeding sites and practice positive behaviors, can be more effective and less costly than the didactic classroom-based sessions. In addition to health education sessions, we will use locally available media, such as loud speakers fixed to local transport, to play songs, street theatre performances, and role playing to reinforce the messages.

#### Adherence

In order to improve adherence to the intervention protocols, CHWs will perform monthly monitoring checks on each HH within the intervention arms. The presence or absence of guppy fish and PPF Sumilarv® 2MR in each container within the HH will be recorded along with any replacements the CHWs provide. The entomology surveys will also record the presence or absence of each intervention in containers (including those used for domestic and non-domestic use) within the surveyed HHs. Project staff will also randomly visit CHWs and intervention HHs to confirm the reliability of data provided.

#### Primary outcome measures

The primary outcome measure is the population density (i.e., number of mosquitoes per unit of time spent aspirating) of adult female *Aedes* trapped using adult resting collections.

#### Secondary outcome measures

The secondary outcomes for the trial include:Dengue virus infection rate in adult female *Aedes* mosquitoesHouse Index (HI): proportion of houses surveyed positive for *Aedes* larvae and/or pupae in any water containerContainer Index (CI): proportion of surveyed containers containing *Aedes* larvae and/or pupaeBreteau Index (BI): number of containers positive for *Aedes* larvae and/or pupae per 100 houses surveyedPupae Per House (PPH): number of *Aedes* pupae per householdPupae Per Person (PPP): number of *Aedes* pupae per personGuppy fish coverage: proportion of eligible water containers with at least one guppy fishSumilarv® 2MR coverage: proportion of eligible water containers with at least one MR diskPercentage of respondents with knowledge about *Aedes* mosquitoes causing dengue

#### Sample size

The guppy fish and PPF interventions will be assessed by an entomology survey. A sample size of 10 clusters per arm and 40 HHs per cluster for the survey was devised using the Hemming and Marsh method [45]. The calculation assumed a mean of 0.1 adult female resting *Aedes* mosquitoes per HH in the intervention arms compared to 0.25 in the control arm for each collection. This assumption was based on the results from the earlier World Health Organization/Asian Development Bank guppy fish project in the same province [22], and to be conservative assumed no impact from the PPF in arm 1. The HHs will be randomly selected at each collection. The intracluster correlation (ICC) was assumed to be 0.01 based on previous studies [46–48]. Additionally, a sensitivity analysis was conducted up to the median value of ICCs for outcome variables (0.03) as found by an analysis conducted by Campbell et al. [49]. Our analysis determined that we would have between 91 to 75% power at ICC values between 0.01 to 0.03. The coefficient of variation in cluster sample size was assumed to be 0.1, and is expected be small as we plan to sample the same number of houses from each cluster. Under these assumptions the study will have 91–75% power to detect a difference at the 5% significance level.

COMBI activities will be evaluated through Knowledge, Attitudes, and Practice (KAP) surveys. A sample size of 10 clusters per arm and 20 HHs per cluster was devised, again using the Hemming and Marsh method [45]. The calculation assumed a 22.5% change in primary outcome indicators from 40 to 62.5% in intervention villages and no change in the control villages over the course of 1 year. Outcome indicators include:Percentage of respondents with knowledge about *Aedes* mosquitoes causing denguePercentage of HHs that keep guppy fish/PPF in water

This calculation was based on the results from the earlier projects done by Malaria Consortium (MC) in the region, and a recent unpublished MC KAP survey completed in six provinces and 30 villages in 2014. The ICC was assumed to be 0.01, and the coefficient of variation of cluster size assumed to be 0.1. Under these assumptions the study will have 90% power to detect a difference at the 5% significance level.

#### Allocation

Clusters will be randomly assigned with a 1:1:1 allocation through a public randomization process. Village chiefs from all clusters and HC chiefs from all HCs will be invited to a central point along with local and national authorities. Locally, the concept of “lucky draw” is very popular, so this method will be used to randomize clusters. Each cluster representative will choose one paper labeled either arm 1, 2, or 3 from a bowl. The numbers on the papers will be printed and concealed by folding the paper in half four times. Three large, labeled sheets of paper will be put on the wall. As each representative selected their study arm, MC staff will write the cluster names on the corresponding sheet.

#### Data collection methods

Data will be collected at 0, 4, 8, and 12 months post intervention, unless otherwise mentioned. The project will employ the following methods:

### Entomology

A baseline survey was conducted prior to start of interventions. An endline survey will be conducted 1 year after the baseline. Two additional surveys during the dry season (4 months post intervention) and light rain (8 months post intervention – peak dengue season) will also be conducted. The schedule of the surveys took into account data from the previous guppy fish project [22]. The survey methodology was developed following the WHO guidelines for entomological collections [1]. Surveys will include indoor adult resting catches and larvae/pupae collection from water containers. The survey team consisted of experienced government staff who received 3 days’ training before beginning. All tools and materials were pre-tested during training. The same team will be used for each entomology survey. Houses within each cluster were selected using a random-number generator [50] applied to the village list managed by the village head.

The adult resting catch will be completed using a battery-powered, portable aspirator (Camtech, Phnom Penh, Cambodia) for 10 min per house in the bedrooms and living spaces, starting in the bedroom and aspirating up and down the wall (from floor to 1.5 m) around the home in a clockwise manner. The mosquitoes will be kept in a screw-top containers inside a cold box and transported to the provincial laboratory for identification to the species level for *Aedes*, otherwise to genus. All *Aedes* mosquitoes will be sexed. After identification they will be stored in a −20 °C freezer and taken to the United States Naval Medical Research Unit 2 (NAMRU-2) in Phnom Penh for confirmation. All *Aedes* females will be pooled and subjected to flavivirus rRT-PCR screening [51]. Flavivirus-positive pools will be further tested for dengue typing by semi-nested RT-PCR assay targeting the C and pre-M regions within the viral genome [52].

Larvae and pupae collection will be completed using the five-sweep net method [53] for containers larger than 50 L. The size of the net is 20 cm by 33 cm. Surveyors will turn the net in an anti-clockwise manner five times, then wait 1 min and perform one sweep from the bottom. This method can sample around 35% of larvae and 31% of pupae, and the total number estimated by an adjustment factor [53]. For containers of less than 50 L, all the water will be poured through the sweep net. All containers within selected HHs will be inspected. All pupae and 10 larvae per container will be put in a plastic bag, labeled (with date and code), and taken back to the laboratory for identification to the species level for *Aedes*, otherwise to genus. After identification they will be taken to NAMRU-2 in Phnom Penh where entomologists will confirm identification of a random sample of 50% of immature mosquitoes.

Survey teams will also record the number, size, and type of all water containers in the HH The team will complete a rapid assessment tool (Premise Condition Index; PCI) [54] to identify whether the scores can predict HH risk for *Ae. aegypti* infestation. If proven useful as an indicator of risk, PCI could be used to streamline future surveys and program activities and possibly reduce program costs.

### Knowledge, attitudes, and practices

The KAP survey was designed around the results of the FGDs and IDIs to create questions based on the local context and language [55]. The KAP will be pilot tested in a neighboring community, and revised where necessary. Questions are close ended or are categorized by data collectors at the time of response.

KAP surveys will be conducted at the same time as baseline and endline entomology surveys. Only the HH head will be asked to respond. The data will be collected by experienced government staff who will be given 2 days’ training before implementation. Each team will have a supervisor who can monitor data integrity and quality. All paper forms are submitted to the MC supervisor who performs a final check making sure that all questions receive a response and that skip patterns are followed correctly.

### Community health worker monthly monitoring

The coverage of guppy fish and PPF Sumilarv® 2MR will be assessed by ocular inspection of water containers via entomology surveys and the CHW monthly reporting form as described in the adherence section. Coverage is expressed as percentage of containers with guppy fish or Sumilarv® 2MR of the total HHs or containers examined.

### Location

The geographical location of each village within the trial and all HHs in the entomology/KAP surveys will be recorded by a handheld Global Positioning System and plotted using ArcGIS® version 10 (Environmental System Research Institute, Redlands, CA, USA) for spatial analysis and for presentation purposes.

### Climate

General climate data (rainfall, temperature and humidity) will be recorded at one of the intervention health centers using a rain gauge and a Hobo onset data logger (all villages have virtually the same climate). Data from the all United States National Aeronautics and Space Administration (NASA) satellites on climate will also be available including air pressure, air temperature, atmospheric moisture, evaporation, precipitation, and wind [56].

### Data management

Double data entry into EpiData (EpiData Association, Odense, Denmark) is completed by an experienced data-entry company. The process of data cleaning is being handled by MC staff. The original forms are kept in a secure, locked cabinet in the MC Phnom Penh office, and will be available during data cleaning and analysis. Surveys will be maintained in storage for a period of 2 years after completion of the study.

### Statistical methods

All statistics will be performed in R (Murray Hill, NJ, USA) and Stata® (College Station, TX, USA).

#### Primary outcome

Adult female *Aedes* density will be summed over follow-up time points to give a single rate per cluster. This will be analyzed by negative binomial regression using the number of adults as the response, and the logarithm of the sampling effort (that is, person-time spent aspirating) as an offset. Hence, this analysis will yield density ratios. The primary analysis will not be adjusted, but secondary analysis will include an analysis adjusted for the baseline density.

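### Negative binomial regression on 30 cluster totals, with no small-sample correction stated, gives a false-positive rate moderately above 5% (about 6–8% per comparison) in its usual output

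*Protocol article*

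**What the plan says.** All references are to the Protocol article.

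- **Unit of analysis** (Primary outcome, under Statistical methods): "Adult female *Aedes* density will be summed over follow-up time points to give a single rate per cluster".
- **Model** (same section): "This will be analyzed by negative binomial regression using the number of adults as the response", with the log of aspirating time as offset. "The primary analysis will not be adjusted"; adjustment for baseline density is a secondary analysis.
- **Number of clusters** (Sample size): "A sample size of 10 clusters per arm and 40 HHs per cluster for the survey was devised". Allocation adds: "Clusters will be randomly assigned with a 1:1:1 allocation through a public randomization process". That makes 30 clusters, 10 per arm.
- **Significance level** (Sample size): 5%. The Discussion says that power was set for each intervention arm against control, so each main comparison is 10 clusters against 10.
- **Software** (Statistical methods): R and Stata.

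The article does not say whether the test is Wald, likelihood-ratio or permutation. It names no t reference and no small-sample correction. The Secondary outcomes section sends the entomological indices and the viral infection rate through the same methods.

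**The concern.** Reducing the data to one total per cluster is sound, because it respects the unit of randomization. It also leaves only 30 observations to estimate three arm means and a dispersion parameter.

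Two features of ordinary negative binomial output then act in the same direction. Maximum likelihood makes no degrees-of-freedom allowance for the fitted arm means, so the fitted variance tends to be too small. The Wald test also refers the result to a normal distribution, although the variance was estimated from few clusters. Standard errors and critical value are both slightly too small.

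At stake is the claim of superiority at the 5% level. A p-value a little below 0.05 would be weaker evidence than it appears, and the intervals for the density ratios would be too narrow. This matters most for a borderline result, for example the contrast between the two intervention arms, which the Discussion admits was not powered.

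**Working it through.** The plan states a nominal 5% level but no achieved false-positive rate, so there is no figure of its own to reproduce on this point.

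**Inputs**

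- Clusters: 3 × 10 = 30 (Sample size, Allocation).
- Follow-up collections: "Data will be collected at 0, 4, 8, and 12 months post intervention" gives three follow-up surveys, so 3 × 40 = 120 household collections per cluster.
- Offset: aspiration lasts "for 10 min per house in the bedrooms and living spaces", so effort is nearly constant across clusters.
- Densities: "0.1 adult female resting *Aedes* mosquitoes per HH in the intervention arms compared to 0.25 in the control arm for each collection".
- ICC: 0.01 to 0.03 (Sample size).
- Assumed, not stated: two-sided test; Poisson counts within cluster unless noted; gamma or log-normal cluster effects.

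**Between-cluster variation.** With Poisson variation within clusters, CV² = ICC / [(1 − ICC) × mean]. At the control mean:

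- ICC 0.01: 0.01 / (0.99 × 0.25) = 0.040
- ICC 0.03: 0.03 / (0.97 × 0.25) = 0.124

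**Simulation under no effect: one arm against control, three-arm fit.** The R column is `MASS::glm.nb` with gamma effects (2,500–3,000 runs per setting). The Monte Carlo standard error is about 0.4–0.5 points.

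| Method | ICC 0.01 | ICC 0.03 |
|---|---|---|
| Wald z, R, gamma effects | 7.3% | 7.7% |
| Wald z, Python, gamma effects | 7.4% | 7.4% |
| Wald z, Python, log-normal effects | 7.6% | 8.3% |
| Uncorrected standard error, t27 (R) | 6.0% | 6.3% |
| Pearson-scaled standard error, t27 (R) | 5.0% | 5.2% |
| t-test on log cluster rates, 18 df (R) | 5.0% | 5.0% |

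Other results:

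- Coverage of the default 95% interval in R was 92.7% and 92.3%.
- The likelihood-ratio test rejected in 6.3–6.6% of runs with gamma effects and 6.8–7.5% with log-normal effects.
- A further simulation of Wald z (5,000 runs per setting) gave 5.9–7.6%, mostly 7.1–7.6%.
- With household overdispersion, or a mean of 0.1, Wald z gave 7.4–8.2%.
- Fits to only the two arms compared (20 clusters) gave 7.6–7.7% with gamma effects and 8.3–8.8% with log-normal effects.
- Across all settings tried, Pearson scaling with t27 gave 4.1–6.3%.

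**Check of the mechanism.** The Pearson chi-square divided by 27 averaged about 1.10 in R, so the fitted variance was about 10% too small; compare 30/27 = 1.11. The true reference is close to t with 27 df:

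- Wald z: 1.96 / √1.10 = 1.87, and P(|t27| > 1.87) ≈ 7.2–7.3%.
- t27 with the uncorrected standard error: 2.052 / √1.10 = 1.96, and P(|t27| > 1.96) ≈ 6.0–6.1%.

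Both agree with the simulation. The 30/27 factor describes the Pearson variance. The dispersion parameter itself averaged 73–87% of its true value, depending on mean and ICC, so no fixed factor applies to it.

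**Cost of correcting.** Width factor: (2.052 / 1.96) × √(30/27) = 1.047 × 1.054 = 1.10. At the planned ratio 0.1/0.25 = 0.4, simulated power was at least 99% under every corrected method (Poisson within cluster).

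**Which labels to permute.** When the other intervention arm worked (ratio 0.4) and the tested arm did not, shuffling all 30 labels rejected in only 0.1–0.7% of trials. At a true ratio of 0.7 and ICC 0.01, power was 34%, against 79% when only the 20 relevant clusters were shuffled.

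**The case against.** The strongest objection is that the article fixes a model, not a test. It names no Wald statistic, normal reference or dispersion estimator. It is also a condensed account, and a statistical analysis plan that is not shown may contain a correction. That stands as a limit: the article does not show that the final analysis will be uncorrected, and nothing in it contradicts itself on this point. It does not remove the point, because the stated model exceeds 5% under either of its usual tests, and a better procedure costs almost nothing.

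A second objection is that the practical effect is small. This also stands. Coverage of 92–93% in place of 95% is a modest shortfall, and at the planned effect the conclusion would not change. Only borderline results are exposed.

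Three stronger readings are tempting and are not supported:

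- **A fixed false-positive rate of 7–8% for the plan.** That range belongs mainly to the Wald z test. The likelihood-ratio test is somewhat lower, and the figure depends on the assumed shape of cluster variation.
- **The same inflation for every secondary outcome.** Only the primary count was simulated. Pupal counts and pooled virus results may behave differently.
- **Any cluster permutation test as the cure.** Shuffling all three arms tests the hypothesis that no arm differs from any other, which is not the comparison of one arm with control.

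**Conclusion.** The point holds in moderate form. Run with standard maximum-likelihood output, the stated primary analysis has a per-comparison false-positive rate of about 6–8% (Wald z) or about 6.3–7.5% (likelihood ratio) against the planned 5%, and its 95% intervals cover about 92–93%.

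This is a simulation result. It rests on a two-sided test, 120 collections per cluster, the protocol's densities and ICC range, and gamma or log-normal cluster effects. Stronger skew would make it worse: log-normal effects with CV² of 0.25 to 1.0, well beyond the planning range, gave 8.9–12.9%. With gamma effects at ICC 0.10 it was 6.6%.

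The stated power of 91–75% is a separate matter and has no bearing on this result.

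**What to change.** Keep the unadjusted negative binomial density ratio as the primary estimate and state how its p-value and interval are obtained. Either of these would do:

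1. Scale the model's standard errors by the Pearson dispersion on 30 − 3 = 27 degrees of freedom and use a t27 reference. A t reference alone is not enough, since it leaves 6.0–6.3%. The correction is close but not exact: about 6% remained at a between-cluster CV² of 0.36.
2. Use a t-test on log cluster rates for each arm against control (18 df), which held 4.7–5.0% in the settings tried. It needs a rule for a cluster with a zero total, which should be rare with about 120 × 0.1 = 12 mosquitoes expected.

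If a permutation test is preferred, permute only the 20 clusters of the two arms being compared. Its interval then has to come from inverting the test.

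Apply the same correction to secondary outcomes that are analyzed as cluster counts, without claiming a particular size of inflation there. If the statistical analysis plan already contains a correction, it is enough to confirm that it covers both the standard error and the reference distribution.

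The cost is a few lines of code, intervals about 10% wider under option 1, and negligible loss of power at the planned effect. Trial status reports only baseline collection, enrollment and allocation as complete, so at that stage the change could be made before any follow-up data were seen.

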### Trial status

At the time of submission of this manuscript the trial had completed the baseline data collections, enrollment of villages, and randomized allocation of the villages to three study arms.

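### The primary density ratio is left unadjusted for a baseline density the trial already holds, which gives up some precision at little saving

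*Protocol article*

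**What the plan says.** Under Statistical methods, Primary outcome, the protocol article reduces the follow-up data to one figure per cluster: adult female *Aedes* "density will be summed over follow-up time points to give a single rate per cluster". The count is modelled by negative binomial regression with log aspiration time as the offset. The same section then fixes the order of the models: "The primary analysis will not be adjusted, but secondary analysis will include an analysis adjusted for the baseline density". It gives no reason. The Secondary outcomes section carries the same methods over to the larval and pupal indices.

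The covariate is in hand. Under Entomology, "A baseline survey was conducted prior to start of interventions", and the surveys described there include the indoor adult resting catch. Trial status reports that "the trial had completed the baseline data collections, enrollment of villages, and randomized allocation of the villages to three study arms". Data collection methods gives the timing: "Data will be collected at 0, 4, 8, and 12 months post intervention, unless otherwise mentioned", that is, one baseline and three follow-up surveys.

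On size and allocation, "A sample size of 10 clusters per arm and 40 HHs per cluster for the survey was devised", and "Clusters will be randomly assigned with a 1:1:1 allocation through a public randomization process". The Allocation section describes the draw of folded papers in some detail and mentions no stratification, matching or restriction.

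**The concern.** With one total per cluster, any lasting difference in mosquito density between clusters falls into the error term of the primary model. A baseline reading of the same quantity could remove part of it. With 10 clusters per arm and an apparently unrestricted draw, the analysis is the only place left to deal with an unlucky split of high- and low-density clusters.

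At stake are the width of the interval around the headline ratio and its robustness. If the two prespecified models disagree, the protocol ties the headline to the one that ignores measured imbalance. The choice is stated outright in the article, so it is not a detail left to an analysis plan.

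**Working it through.** **Inputs from the article (Sample size).** 10 clusters per arm; m = 40 households per cluster per survey; means 0.25 (control) and 0.1 (intervention); ICC 0.01, with sensitivity to 0.03; CV of cluster sample size 0.1; 5% level, taken as two-sided; stated power 91% to 75%. Households are drawn afresh ("The HHs will be randomly selected at each collection"), so baseline can enter only at cluster level.

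**Inputs not in the article (assumptions).** The outcome SD, and how far cluster differences persist between surveys (cluster autocorrelation, CAC). CAC is shown over a range.

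**Step 1. The stated power.** Design effect = 1 + ((0.1² + 1) × 40 − 1) × ICC = 1.394 at ICC 0.01 and 2.182 at ICC 0.03. Effective n per arm = 400/1.394 = 286.9 and 400/2.182 = 183.3. A two-means calculation needs an SD, and 0.545 reproduces both ends:
- ICC 0.01: 0.15/(0.545 × √(2/286.9)) = 3.30; Φ(3.30 − 1.96) = 90.9%.
- ICC 0.03: 0.15/(0.545 × √(2/183.3)) = 2.63; Φ(2.63 − 1.96) = 75.0%.

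The SD of 0.545 is therefore back-solved, not printed. These powers refer to one collection, whereas the primary analysis sums three.

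**Step 2. Baseline to follow-up correlation.** In units of total variance:
- baseline cluster mean: Vb = ICC + (1 − ICC)/40
- sum of three follow-ups: Vf = ICC × (1/3 + 2/3 × CAC) + (1 − ICC)/120
- r = ICC × CAC/√(Vb × Vf)

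Example, ICC 0.03 and CAC 1: Vb = 0.05425, Vf = 0.03808, r = 0.03/√(0.05425 × 0.03808) = 0.66.

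**Step 3. Effect on variance.** Factor = (1 − r²) × 26/25, where 26/25 = 1 + 1/(30 − 3 − 2) is the small-sample cost of one covariate in 30 clusters with three arms. The planned negative binomial model was also simulated with and without log baseline density (900 runs per setting, density ratio 0.40, log[(count + 0.5)/40] as covariate).

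| ICC | CAC | r | Factor, formula | Factor, simulated |
|---|---|---|---|---|
| 0.01 | 0 | 0 | 1.04 | 1.03 |
| 0.01 | 0.5 | 0.22 | 0.99 | 0.98 |
| 0.01 | 0.8 | 0.33 | 0.93 | 0.95 |
| 0.01 | 1 | 0.40 | 0.88 | 0.93 |
| 0.03 | 0 | 0 | 1.04 | 1.02 |
| 0.03 | 0.5 | 0.38 | 0.89 | 0.86 |
| 0.03 | 0.8 | 0.56 | 0.72 | 0.75 |
| 0.03 | 1 | 0.66 | 0.59 | 0.67 |

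For CAC 0.5 to 1 the formula gives a 1-12% reduction at ICC 0.01 and 11-41% at ICC 0.03; simulation gives 2-7% and 14-33%. With no persistence the cost is 2-4% here; allowing up to 5% covers other simulated settings. Both models centred on the true ratio (0.395 to 0.403).

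**Step 4. Chance imbalance.** Between-cluster CV = √ICC × 0.545/0.25 = 0.218 and 0.378. The SD of the log ratio of true baseline density between two arms of 10 is √ln(1 + CV²) × √(2/10) = 0.096 and 0.163. The 95% chance range of that ratio is 0.83-1.21 (ICC 0.01) and 0.73-1.38 (ICC 0.03).

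**Step 5. What this means at the planned effect.** The target ratio is 0.1/0.25 = 0.4, and ln 0.4 = −0.916. In the least favourable simulated setting (ICC 0.03, CAC 1) the SD of the log ratio is 0.213 unadjusted and 0.175 adjusted. Unadjusted: 0.916/0.213 = 4.30 and Φ(4.30 − 1.96) = 99%, so power is near 100% with either model. The interval does change: around 0.40 it runs about 0.26-0.61 unadjusted (factor e^(1.96 × 0.213) = 1.52) and 0.28-0.56 adjusted (factor 1.41).

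**Step 6. Smaller effects (assumed, not in the article).** For a 34% reduction against control at CV 0.38, simulated power (400 runs) rose from 58% to 65% with autocorrelation 0.7 and from 62% to 78% with full persistence. For arm 1 v arm 2 with an assumed further 34% reduction, it rose from 47% to 58% at CV 0.38 with full persistence. It was flat (48% to 49%) at autocorrelation 0.5, and nearly so (64% to 66%) at CV 0.22 with full persistence.

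**The case against.** The strongest reply is that nothing here is wrong. An unadjusted cluster-level comparison in a randomised trial is valid, and the adjusted model is already prespecified, so readers will see both. That stands, and it limits the point to which model carries the headline.

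The second reply concerns size, and it also largely stands. A reader might take the fall from 91% to 75% as proof that the primary analysis is short of power. Those figures are for a single collection of 40 households per cluster, while the primary analysis sums three. A reader might also quote large power gains, but these need an effect well below the planned 60% reduction, and no such effect appears in the article. The upper ends of the variance ranges need cluster differences to persist fully. The Entomology section places the follow-ups in the dry season, in the light rains and one year after baseline, so full persistence is not a safe default.

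Third, a reader might infer that any baseline imbalance passes whole into the density ratio. It passes only as far as cluster differences persist, and the unadjusted standard error already reflects between-cluster variation.

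Finally, baseline and allocation were complete at submission, so a switch now could be made with the imbalance in view. This carries little weight, because the adjusted model and its covariate are already named in the protocol and no follow-up outcome need be seen.

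**Conclusion.** The point holds as a matter of precision and robustness, not as an error. The documents do not support calling the unadjusted ratio biased or the trial underpowered at its planned effect.

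The gain is close to nil to modest at the planning ICC (1-12% of variance) and material at the upper ICC (11-41%). The possible loss is about 2-5%. These figures rest on the back-solved SD of 0.545 and on a CAC of 0.5 to 1, neither of which the article states. At 0.25 v 0.1 the benefit is a narrower interval. More power can be expected only for effects smaller than planned, or possibly for arm 1 v arm 2, which the Discussion concedes was not powered. Because the possible gain exceeds the possible loss and the covariate is already collected, adjusting is the better default. Severity is minor to moderate.

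**What to change.** Before any follow-up data are analysed, exchange the two models. Make the negative binomial regression with log baseline cluster density the primary analysis, with a small stated constant added for clusters with zero baseline counts (0.5 was used in the working above). Keep the unadjusted density ratio as a sensitivity analysis. Record that the change was made on design grounds and without sight of follow-up outcomes.

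The cost is one sentence in the protocol or analysis plan and one degree of freedom. No new data are needed.
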